### Study population

All patients at the participating clinics that fulfil the inclusion and exclusion criteria described below shall be assessed whether they can be included in the study. To further illustrate patient selection, data on all patients with rectal cancer who are continously registered in the Swedish ColoRectal Cancer Registry (SCRCR), will be reviewed and evaluated retrospectively to find out how many were not included in the study (exclusions or missing) and possibly reasons for this.

Inclusion criteria:Age 18 years or older.Proven rectal cancer by biopsy.Tumour 5 cm or higher from the anal verge, and a Hartmann’s procedure is assessed to be locally curative.Both operations should be performable.Impaired functional capacity and/or severe co-morbidity where an anterior resection and anastomosis is deemed very risky.Impaired sphincter function and where an anterior resection is deemed not suitable.Surgery may be palliative but shall be assessed to be locally radical.

Exclusion criteria:Rectal cancer below 5 cm from the anal verge.Patients in whom a low anterior resection is considered suitable.ASA IV/V.Non-correctable coagulopathy.

### Primary investigation prior to randomization

Medical history: co-morbidities, smoking, dementia, sphincter function, WHO performance scale.

Survey: digital rectal examination, rigid rectoscopy, colonic examination, CT scan of lungs and abdomen (or ultrasound liver and plain chest X-ray if certain renal insufficiency) and MRI of the rectum.

Consecutive patients examined for rectal cancer as above, will be evaluated for their suitability for inclusion in the studie. After all inclusion and exclusion criteria have been verified, the patient will be informed about the trial at the outpatient clinic and informed consent will be obtained.

### Protocols

#### Inclusion protocol and collected data

To be completed at inclusion. Patients that are eligible for inclusion - but are not included - are recorded, stating the reason for exclusion. This is to seek control of selection bias. If the patients themselves choose not to participitate the reason for this may not be asked.

At the outpatient clinic, the patient is also asked to participate in a study concerning quality of life. This study is managed separately from the Department of Surgery, Sahlgrenska University Hospital/Östra, Sweden (NCT01477229).

### Registration protocol and collected data

Data on medical history, the medical work-up, laboratory data and operative data that are not collected in the SCRCR peroperative protocol, are recorded.

The following variables are recorded: age, sex, weight, height, ASA grade, WHO performance, dementia, symptoms, fecal incontinence, smoking, tumour location and height, TNM stage according to MRI, tethering of the tumour according to rectal exploration, presence of metastas, laboratory tests (albumin, CRP, WBC, Hb), previous radiotherapy, neo-adjuvant oncological treatment. Type of surgery, tumour location visavi peritoneal reflection, ligation of inferior mesenteric artery or not, skill level of the surgeon, width of bowel stapler (mm), make of surgical stapler, operation time, bleeding, associated peri-operative complications, ano-rectal stump divided or not in intersphincteric APE.

### Participating clinics and surgeons

During the last decades, rectal cancer surgery in Sweden has been concentrated to not more than one hospital in most counties with a catchment area around 250 000 or more. All hospitals in Sweden that perform surgery on patients with rectal cancer have the opportunity to participate in the study. According to the decision of the Regional Ethics Council in Uppsala (No: 2013/297), applications from the following research principals were accepted:

County Region of Västmanland, County Region of Värmland, County Region of Gävleborg, County Region of Uppsala, County Region of Västra Götaland, County Region of Östergötland, County Region of Sörmland, County Region of Västernorrland, Region Scania, County Region of Örebro and Stockholm County Region.

The trial will be conducted at six university hopitals and 12 county hospitals.

Experience in total mesorectal excision (TME) is demanded for surgeons taking part in the trial. If the operation is performed laparoscopically assisted, the surgeons should be experienced in this technique.

### Randomization

The patients will be fully informed preoperatively orally and in writing and will have to sign an informed consent. We will explain pros and cons about the two types of operations and that we don’t know which one is the most appropriate and that we will make the randomisation during the operation. The patients are fully aware and have accepted this procedure if they are included in the study. This procedure was chosen to avoid bias in the selection of patients as regard the type of surgery. If you randomize before surgey then some surgeons could chose to not to include some patients because they want to perform one of the two types of surgery that they believe is easier, better or goes faster. This is the point, we don’t know which of the two types of surgery that is most appropriate for the patient because there exists no data or comparative studies. That’s why it is so important to randomisze during surgery to avoid this selection. Our Ethics committee in Uppsala have accepted this procedure.

The randomization procedure is performed in the operation theatre when the TME has been performed, the distal bowel tube has been clamped and a washout of the anorectum performed.

Randomization is performed per center by a central automated internet randomization module through the website ”www.norrlandskirurgi.se” and stratified for each centre. The website includes all necessary information and protocols.

### Surgery

#### The operation, common to both surgical procedures

An experienced TME surgeon participates. The patient is stoma-marked pre-operatively by a trained nurse. Antibiotic prophylaxis, thrombosis prophylaxis, continuous thoracic epidural and laxatives are administered according to local practice. The patient is positioned with lowered leg supports.

The abdominal dissection is performed with a high or low ligation of the inferior mesenteric artery,dissection along the rectal mesentery, performing a total mesorectum excision down to the pelvic floor. A bowel clamp is applied below the tumour and the rectum is rinsed according to local practice. A suitable stapler is placed distally below the bowel clamp. The stapler is closed without fireing. The stapler is left in place. Now randomization is performed using the trial website. According to the results of the randomization (HP or APE with ID), the procedure is continued.

### Arm 1

#### Resection of the rectum with distal closure and colostomy (Hartmann)

The stapler is fired and the tumour-bearing bowel specimen is removed. The distal colon is brought out as an ostomy on the abdominal wall via the rectus muscle. One or two passive drainages are applied in the pelvis. The abdominal fascia is closed with a suture quota of > 4:1.

### Arm2

#### Abdominoperineal resection with intersphincteric dissection (APE + ID)

Depending on personal experience, the stapler is fired without cutting the intestine, or the staple is fired and the bowel cut and the tumour-bearing bowel specimen removed. Thereafter an intersphincteric dissection of the ano-rectal stump is performed. In the first option ID is performed with the entire tumour-bearing bowel intact, in the latter ID is carried out after the bowel specimen is removed. The surgery continues with the patient preferably in a lithotomy position. Again, the anus is carefully washed and the anus is sealed tightly with two purse-string sutures. The skin in the inner edge of the external sphincter is incised, and the dissection is carried out in the intersphincteric plane up along the external sphincter, levator muscles and the puborectalis sling and into the pelvis. The specimen is either removed through the perineum or the abdomen, depending on whether you have stapled off the rectum distally or not, see above. The puborectalis, the levator and the external sphincter and the perineal skin, are sutured from the inside out. The distal colon is brought out as an ostomy on the abdominal wall through the rectus muscle. One or two passive drainages are applied in the pelvis. The abdominal fascia is closed with a suture quota of > 4:1.

### Laparoscopic/robotic assisted surgery

Surgeons experienced in laparoscopic TME participates. Surgery is performed as in the open technique with TME dissection down to the levator. The rectum is closed distal to the tumour with a laparoscopic Satinský or an angled 45 mm stapler. Alternatively, the abdomen is opened with a Pfannenstiel incision above the pubic bone and the same clamping procedure as in open surgery is performed. After a rectal washout, the patient is randomized via the trial website, see above.

### ARM 1

If randomized to HA: transect the bowel with the laparoscopic stapler below the Satinský, or transect with cutting stapler below the non-cutting stapler - or alternatively transect through a Pfannelstiel incision and cut the bowel with knife above the stapler - and remove the specimen through an abdominal incision.

### ARM 2

If randomized to APE with ID, the bowel can be transsected with the laparoscopic stapler below the clamp, or transected with a cutting stapler below the non-cutting stapler –or alternatively transected through a Pfannelstiel incision and the specimen removed via the abdominal incision. ID is then performed as described above in the ARM 2 open procedure, with the patient in a lithotomy position. The anorectal specimen is taken out through the perineal wound.

### Follow-up and collected data

The study intends to map the post-operative course. Follow-up examinations are performed 1 month after discharge and, if necessary, continuously until the healing is complete. An additional follow-up is performed after 12 months with symptom score and quality of life evaluation. All patients are monitored annually for another 4 years according to the SCRCR protocol.

### Follow-up protocol - 30 days

All surgical complications and interventions in the post-operative course are recorded. At the outpatient clinic 4 weeks after surgery, the patient is re-examined and the 30-day follow up protocol is completed. Specific complications are registered such as abdominal wound infection, perineal wound infection, pelvic abscess, pus-secretion through the anus, proctitis (patients will be examined with proctoscopy), fistula, stomal complications, bowel obstruction, urinary catheter at discharge, cardio-vascular and other infectious complications. All measures taken due to surgical complications are registered, including small surgical or other interventions such as radiological drainage or drainage transanally. Antibiotic therapy during the hospital stay, length of stay and re-admissions will be recorded.

### Follow-up protocol - 1 year

Late local complications and possible problems with infection or pain in the perineal or pelvic area or disorders such as secretion or bleeding from the anorectum, are recorded 1 year after surgery (proctoscopy). Other data are registered in the SCRCR protocol. At this time, the patient’s perceived quality of life is investigated using a separate protocol to be completed by the patient.

After the 1-year follow-up, patients are followed according to the SCRCR protocol with annual controls registering local recurrences, metastases and death.

### Sample size considerations and statistics

The literature describes a surgical complication rate of approximately 35 % after a HP. Most of these complications are pelvic abscesses whereas after an APE the most frequent complication is a perineal infection. By performing an intersphincteric dissection, we believe that the perineal complication rate will be significantly lowered. We assume that the surgical complication rate can be reduced to 20 % with an intersphincteric APE. With a type I error of 0.05 (α) and a power of 0.8 (1 - β (0,2)), 140 patients in each group are needed. With a drop-out estimate of 20 %, the required sample size is 170 patients in each group. A research fellow will monitor the data of all included patients together with the consultants responsible for the study. A SPSS database will be used containing all collected parameters. Data analysis will be performed according to intention-to-treat protocol analysis, an additional per-protocol analysis will also be performed. The primary endo-point measure will be evaluated using chi-squared test. Continuous variables will be compared with a T-test or Mann-Whitney U where appropriate. Differences with a *P-*value <0.05 will be considered statistically significant. All the statistical analysis will be conducted by using SPSS version 22 software (SPSS, Inc., Chicago, IL, USA).

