### Primary endpoint

The primary objective of this trial is to observe the rate of local surgical complications (as graded by the Clavien-Dindo scale) within 30 days.

Secondary endpoints:Frequency of intra-operative rectal perforations.Duration of operation.Amount of blood loss.Re-operation and re-intervention (eg, percutaneous and transanal drainage) rate.Post-operative length of hospital stay.Re-admission frequency.Histology with TNM-status and resection margins.Local recurrence and metachronous distant metastasis rate.Survival after 3 and 5 years.Quality of life 1 year after surgery.Late local complications from the perineum or ano-rectal area within 1 year follow-up.

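### Randomization is stratified by centre but the primary chi-squared test is not: the test is valid and keeps its planned power, but a centre-stratified test could give more power at little cost

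*Protocol article*

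**What the plan says.** Under Randomization, the article states that "Randomization is performed per center by a central automated internet randomization module" and that it is "and stratified for each centre". No block size or other balancing method is given. Under Participating clinics and surgeons: "The trial will be conducted at six university hopitals and 12 county hospitals", which makes 18 strata.

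The primary endpoint is "the rate of local surgical complications (as graded by the Clavien-Dindo scale) within 30 days". Under Sample size considerations and statistics, the plan for it is: "The primary endo-point measure will be evaluated using chi-squared test". No stratum, covariate or centre term is named.

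The sample size in the same section rests on two rates: "The literature describes a surgical complication rate of approximately 35 % after a HP" and "We assume that the surgical complication rate can be reduced to 20 % with an intersphincteric APE". It uses a 5% type I error and 80% power, and arrives at 140 per group, raised to 170 for drop-out.

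**The concern.** The stratification used to allocate patients does not appear in the analysis. Balancing the arms within centres removes centre differences from the comparison of arms. The pooled chi-squared variance still counts those differences as noise. If centres differ, the standard error is then larger than it need be, the test rejects less than 5% of the time under the null, and some power is left unused.

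The article gives reasons to expect some centre variation. Prophylaxis, bowel preparation and rectal washout are left to each centre, arterial ligation may be high or low, open and laparoscopic or robotic routes are both allowed, and surgeon skill and stapler type are recorded as variables. It gives no figure for how far complication rates differ between centres. What is at stake is efficiency in a frail population that is hard to recruit, not the validity of the result.

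**Working it through.** **1. The plan's own figure.** Inputs from the statistics section: 35% vs 20%, alpha 0.05 (sidedness not stated, taken as two-sided), power 0.80, 1:1 allocation. The endpoint is treated as a yes/no outcome, as the calculation and the test imply. With mean rate 0.275:

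n = [1.96 × √(2 × 0.275 × 0.725) + 0.842 × √(0.35 × 0.65 + 0.20 × 0.80)]² / 0.15² = 137.9, so 138 per group.

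The stated 140 is reproduced and gives 80.6% power. This is the sample size of an unstratified two-proportion test, so the planned power belongs to the test the article names.

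**2. The two tests.** For centre k, let n1k and n0k be the arm sizes, nk their sum, x1k the events in arm 1 and mk all events.

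- Pooled chi-squared: (p1 − p0)² / [p(1 − p)(1/N1 + 1/N0)], with all centres merged.
- CMH, without continuity correction: [Σ(x1k − n1k·mk/nk)]² / Σ[n1k·n0k·mk(nk − mk) / (nk²(nk − 1))].

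The second removes differences between centres from the variance; the first does not.

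**3. Assumed centre variation.** Each of 18 centres gets a normal random effect on the logit scale, with the overall rates held at 35% and 20% (27.5% in both arms under the null). The range that would hold 95% of centres' Hartmann rates, around an average of 35%, is:

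- SD 0.5: about 16% to 58%
- SD 0.8: about 9% to 70%
- SD 1.0: about 6% to 77%
- SD 1.2: about 4% to 83%

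**4. Results (chi-squared vs CMH).** Three allocation settings, all assumed because the article states none:

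- A: exact pairs within centre, unequal centres, 280 analysed for power and 340 for type I error.
- B: blocks of 4, centres of equal expected size, 280 analysed.
- C: blocks of 4, 340 randomized, 18% random drop-out (340 × 0.82 = about 279 analysed).

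| SD | Power, A | Power, B | Power, C | Chi-squared type I error |
|---|---|---|---|---|
| 0 | – | 81.0 vs 80.6 | 80.0 vs 78.8 | 5.2 (B), 4.9 (C) |
| 0.3 | – | 82.5 vs 82.6 | – | 5.0 (B) |
| 0.5 | 82.3 vs 83.1 | 80.9 vs 81.8 | 81.3 vs 81.7 | 4.7 (A), 4.3 (B) |
| 0.8 | 82.6 vs 84.8 | 82.6 vs 84.9 | 81.0 vs 83.4 | 4.0 (A, B) |
| 1.0 | – | 83.3 vs 86.7 | – | 3.2 (B) |
| 1.2 | 83.2 vs 88.3 | – | 82.6 vs 88.1 | 3.1 (A), 3.6 (C) |

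All entries are percentages. With the 6,000 runs per scenario of A and B, Monte Carlo error is about √(0.8 × 0.2/6000) = 0.5 points on power and √(0.05 × 0.95/6000) = 0.3 points on type I error. CMH type I error stayed near 5%.

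**5. Without blocking.** If each patient is allocated independently within centre, chi-squared type I error stays near 5% even at SD 1.2 (4.6% to 5.0%), so the conservatism disappears. With no centre effect, CMH then costs about 2 points of power. A further run (340 randomized, 18% drop-out, six centres three times the size of the other 12, 8,000 runs) gave 80.6% vs 77.7%, so the cost can approach 3 points.

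**The case against.** The strongest case against the point has four parts.

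- **Nothing planned is lost.** The 140 per group was computed for the unadjusted test, and chi-squared power was at or above 80% in every scenario tabulated. This stands. A reader might infer that the trial is underpowered because of its test, and the article does not support that: what is forgone is power above the plan.
- **The size rests on an assumption.** The article gives no between-centre variation. Its Discussion cites pelvic abscess rates from 3% to 33%, but these come from small retrospective series with different case mix and do not measure centre differences under one protocol. With no centre effect nothing is gained, and SD 1.2 implies an extreme spread. This stands, so the effect must be stated conditionally.
- **Balance within centre is not documented.** Stratified allocation without blocks or a similar device does not guarantee it, and the conservatism depends on it. This stands too.
- **Centre adjustment may sit in an analysis plan that is not shown.** This stands only in part. The article does not leave the primary test open. It names one, and that test omits the factor used in randomization. If an analysis plan already stratifies, the two texts need to be reconciled.

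These arguments reduce the size of the point. They do not remove the mismatch between the stated design and the stated test.

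**Conclusion.** The point holds as a minor efficiency matter. The stated chi-squared test is valid. A reader might infer that ignoring the strata inflates false positives or makes the standard error wrong in every case. Neither follows: any error is on the conservative side, and it is absent if centres do not differ or if allocation is not balanced within them.

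If centres do differ and allocation is blocked, a stratified test gains about 0 to 1 point of power for SDs up to 0.5, about 2 points at 0.8 and about 5 points at 1.2, and brings the type I error back to about 5%. These figures rest on the article's 35% and 20% and 18 hospitals, and on assumed centre SDs, block sizes and centre sizes. The lower part of the range already covers wide differences between centres, so a gain of 2 points or less is the more cautious expectation.

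**What to change.** In the statistics section, replace the sentence on the primary test. Make the primary analysis a CMH test stratified by centre, and state whether a continuity correction is used. Report with it the Mantel-Haenszel risk difference, Σ[(n1k·n0k/nk)(p1k − p0k)] / Σ(n1k·n0k/nk), and its 95% CI. Keep the plain chi-squared test as a sensitivity analysis. State the block size or other balancing method at least in the analysis plan.

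Centres will average 280/18 = about 16 to 340/18 = about 19 patients, and some will be much smaller. Any pooling of very small centres should follow a rule fixed before the analysis and without sight of outcomes by arm, because pooling departs from the randomization strata.

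The change takes a few sentences, with no extra data or patients. Its downside arises if centres do not differ: up to about 1 point of power with blocked allocation, and about 2 to 3 points without.

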The alternative to a low HP would be to perform an abdominoperineal excision (APE) to avoid leaving a suture line on the rectum stump left in the pelvis, in order to reduce the risk of a suture line insufficiency which migth lead to a pelvic abscess. However, the problem with APE is that perineal necrosis and wound infections are common, with perineal wound problems ranging between 15 and 38 %, the latter after neoadjuvant radiotherapy [11]. This can probably be reduced to a large extent, especially after radiotherapy,by removing the anus with an intersphincteric dissection (ID), ie the muscular pelvic floor and external sphincter are left in situ. This means that one can seal the perineum with healthy muscle tissue, which improves healing as opposed to the traditional APE with sutures in the fatty tissue. Moreover, fat tissue suturing is often problematic as APE creates a large wound that is difficult to close, leaving blood/fluid cavities, which further increase the risk of infection. Intersphincteric proctectomy has been used for inflammatory bowel diseases such as Crohn’s disease and ulcerative colitis, and offers significantly less perineal defects than the traditional APE [12–14]. Whether an intersphincteric APE is better than HP in rectal cancer patients with regard to postoperative complications is unclear, although there are theoretical advantages. There are no published papers on the subject or on intersphincteric APE practised in rectal cancer patients, only a few abstracts that suggests low post-operative surgical complication rates after intersphincteric APE.

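### The primary chi-squared test leaves out centre and previous radiotherapy; adjusting for both would be a modest gain in precision, not the repair of an error

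*Protocol article*

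**What the plan says.** - **Endpoint** (Protocol article, Primary endpoint). The aim is to "observe the rate of local surgical complications (as graded by the Clavien-Dindo scale) within 30 days".
- **Primary test** (Sample size considerations and statistics). "The primary endo-point measure will be evaluated using chi-squared test". The analysis is by intention to treat, with an additional per-protocol analysis. No covariate or stratified analysis is named.
- **Sample size** (same section). The rate after Hartmann's procedure is put at about 35%. For the other arm: "We assume that the surgical complication rate can be reduced to 20 % with an intersphincteric APE". Alpha 0.05 and power 0.80 give 140 per group, raised to 170 to allow for 20% drop-out.
- **Randomisation** (Randomization). It takes place in theatre after the mesorectal dissection and is stratified by centre only. Six university and 12 county hospitals are planned (Participating clinics and surgeons), 18 in all.
- **Radiotherapy.** The Background gives perineal wound problems after conventional abdominoperineal excision as 15 to 38%, "the latter after neoadjuvant radiotherapy". It then expects intersphincteric dissection to lessen the problem, above all in irradiated patients. The recorded variables include "previous radiotherapy, neo-adjuvant oncological treatment" (Registration protocol and collected data).

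**The concern.** The article does not leave the primary test open: it fixes a crude two-by-two comparison. Two pieces of baseline information are at hand and unused. Centre is the stratification factor, and a test that ignores it discards whatever precision the stratification bought. Radiotherapy is the one patient factor that the article itself connects with a high rate of perineal wound problems, and it is already collected.

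At stake is precision. If a baseline factor predicts the outcome, adjusting for it removes its chance imbalance from the estimated difference and can raise power at the same sample size. That has some value here, because the planned size leaves little reserve once the expected drop-out occurs.

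**Working it through.** **1. The plan's own figure.** Inputs: 35% and 20%, alpha 0.05 (taken as two-sided), power 0.80. Mean risk is (0.35 + 0.20)/2 = 0.275.

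n = [1.96·√(2·0.275·0.725) + 0.842·√(0.35·0.65 + 0.20·0.80)]² / 0.15² = [1.238 + 0.524]² / 0.0225 ≈ 138 per group.

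This agrees with the stated 140. Power is 80.6% at 140 per group. Losing 20% of 170 leaves 136, with 79.4% power. The crude test therefore delivers roughly the power claimed for it.

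**2. Power with and without adjustment for radiotherapy.** Assumptions: 30%, 50% or 70% of patients irradiated (the article gives no figure) and a risk ratio of 38/15 = 2.53 for radiotherapy. Overall risks are held at 35% and 20%, with 140 per arm. The crude chi-squared test was compared by simulation with a Mantel-Haenszel test stratified by radiotherapy, using 20,000 trials per scenario. The simulation error of each power figure is about √(0.81·0.19/20,000) = 0.3 points.

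| Irradiated share | Both arms: crude | Both arms: stratified | Excision arm only: crude | Excision arm only: stratified |
|---|---|---|---|---|
| 30% | 81.4% | 84.7% | 81.1% | 81.3% |
| 50% | 81.1% | 83.6% | 81.3% | 81.6% |
| 70% | 81.1% | 82.5% | 81.0% | 80.7% |

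Allowing for simulation error, the gain is about 1.5 to 3.5 points if radiotherapy acts in both arms and nil if it acts only in the excision arm. With equal overall rates, type I error is 5.2% crude and 5.0 to 5.1% stratified.

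**3. Chance imbalance.** The SD of the difference in irradiated share between arms is √(2·p·(1−p)/140): 5.5 points at p = 0.3 or 0.7, and 6.0 points at p = 0.5. If the full gradient of 38 − 15 = 23 points held in both arms, one SD would move the estimated difference by 0.055·23 = 1.3 to 0.060·23 = 1.4 points, against a target of 15.

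**4. Variance removed by adjustment, half irradiated (assumption).**
- Full 23-point gradient in both arms: 0.25·0.23² / (0.265·0.735) = 0.068, or 0.068·340 ≈ 23 patients.
- Excision arm only, 20% overall, ratio 38/15: the risks are 0.20/(0.5 + 0.5·2.53) = 11.3% and 28.7%. The slope averaged over arms is (28.7 − 11.3)/2 = 8.7 points. Then 2·0.087²·0.25 / (0.20·0.80 + 0.35·0.65) = 0.0098, or about 3 of 340 patients.

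**5. Centre.** The article gives no variation between centres, so no gain can be computed. In simulation, stratifying by 18 equal-sized centres cost no power. Sparseness still matters: 340/18 ≈ 19 patients per centre, and 280·0.275 = 77 expected events against about 20 parameters in a logistic model with fixed centre effects (intercept, arm, radiotherapy, 17 centre terms). Crossing centre with radiotherapy makes 36 cells of about 280/36 ≈ 8 patients. Cells that hold one arm only contribute nothing.

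**The case against.** The strongest case against is that nothing here is wrong. Radiotherapy precedes randomisation, so the unadjusted intention-to-treat test is unbiased, its 5% level already covers chance imbalance, and it matches the basis of the sample size. Adjusted analyses are also often left to an analysis plan, which is not shown. The validity argument stands in full. The last argument stands in part: supportive analyses may well be described elsewhere, but the article does name its primary test, and that stated choice can be improved.

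Three stronger readings are tempting, and the article does not support them.

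- *That the 15 to 38% gradient applies to this trial.* It describes conventional excision, which is neither arm. The article expects the intersphincteric technique to reduce the problem especially after radiotherapy, and Hartmann's procedure leaves no perineal wound. The endpoint is also wider than perineal wounds. A saving of 23 patients therefore needs the full gradient in both arms and is an upper bound. The implied mean risk of 26.5% also sits above the 20% assumed for the intersphincteric arm.
- *That adjustment is free.* Eighteen fixed centre effects may be too many for the expected events, so the method needs care.
- *That radiotherapy is recorded before randomisation.* The treatment comes first, but the article does not say when the form that records it is completed.

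A factor that acts mainly in one arm is a possible effect modifier, and adjusting for its main effect then gains nothing. That would argue for an interaction analysis, which would have low power here.

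**Conclusion.** The point holds as a modest improvement in efficiency. The crude chi-squared test is valid and has about the power claimed. Leaving out radiotherapy forgoes between nothing and about 3.5 points of power. Where in that range depends on the irradiated share and on whether radiotherapy affects complications after both operations, and the article informs neither. The gain from including centre cannot be quantified from the article; the case for it rests on following the stratified design. A reader might infer that the primary result would be biased or its error rate inflated. Neither follows.

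**What to change.** Before any comparison by arm, pre-specify as the primary analysis one adjusted for previous radiotherapy (yes/no) and centre, by a method that tolerates small centres. Options are a logistic model with centre as a random effect or with small centres pooled by a rule set in advance, or Mantel-Haenszel stratification. With the latter, small centres should be pooled, because crossing all 18 with radiotherapy could give back the gain. Report a risk difference with 95% CI, and keep the chi-squared test as a sensitivity analysis. State that radiotherapy status is taken from information that predates the operation. An arm-by-radiotherapy interaction is optional and should be labelled exploratory and low-powered.

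The cost is a change of wording, slightly more analysis work and the rule for sparse centres. It needs no new data and no larger sample.

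### Operating time, blood loss and length of stay are compared without adjustment for surgical approach, a pre-randomization factor; the tests are valid but may be less precise than they could be

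*Protocol article*

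**What the plan says.** The statistics section of the protocol article gives one rule for all continuous outcomes: "Continuous variables will be compared with a T-test or Mann-Whitney U where appropriate". Neither test takes a covariate. The secondary endpoints listed under the primary endpoint heading include "Duration of operation.Amount of blood loss" and "Post-operative length of hospital stay".

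Open surgery and laparoscopic/robotic assisted surgery are both admitted. Of the latter the article says "Surgery is performed as in the open technique with TME dissection down to the levator".

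Allocation comes late in the operation: "The randomization procedure is performed in the operation theatre when the TME has been performed, the distal bowel tube has been clamped". The laparoscopic/robotic section agrees: "After a rectal washout, the patient is randomized via the trial website, see above". Allocation is stratified by centre and by nothing else.

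The list of registered variables includes "Type of surgery, tumour location visavi peritoneal reflection". It does not say whether the first of these items means the approach or the procedure (Hartmann or intersphincteric excision).

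**The concern.** By the time a patient is randomized, the choice between open and minimally invasive surgery has been made and the mesorectal dissection is done. Allocation cannot influence approach at that moment, so adjusting for it introduces no bias. The three endpoints may plausibly depend on approach, although the documents do not say so. If they do, an unadjusted test leaves all the between-approach variation in the error term.

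The intra-operative timing gives this more weight than a routine call for covariates. If the recorded operating time and blood loss cover the whole operation, part of each value accrues before allocation and carries no information about the arms. Approach is an obvious candidate source of that noise. The Discussion names longer surgery as a disadvantage of the intersphincteric procedure, so the size of that penalty is something readers will want estimated well. What is at stake is the width of the confidence intervals for three secondary endpoints.

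**Working it through.** **The plan's own figure.** The only sample size stated is for the binary primary endpoint: 35% versus 20%, α 0.05, power 0.80, 140 per group. With the two-sided pooled formula,

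n = [1.96·√(2·0.275·0.725) + 0.8416·√(0.35·0.65 + 0.20·0.80)]² / 0.15² = (1.2377 + 0.5239)² / 0.0225 ≈ 138.

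This reproduces 140 closely (power at 140 is 80.6%), and the present point does not touch it. No SD, approach mix or effect of approach is given for the continuous endpoints, so what follows rests on assumptions. Only operating time is worked in minutes.

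**Assumed inputs.** Within-approach SD 60 min; share of minimally invasive surgery p = 0.20 to 0.50; mean difference between approaches d = 30 to 90 min. From the plan: 140 analysed per arm.

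**Formulas.**
- Between-approach variance = p(1−p)d²
- Total variance = 60² + p(1−p)d²
- Equivalent gain in patients = total / 60² − 1
- SE of the mean difference = √(2·variance / 140)

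| p | d (min) | p(1−p)d² | Total variance | Share of variance | Gain in patients | SE unadjusted | SE adjusted |
|---|---|---|---|---|---|---|---|
| 0.20 | 30 | 144 | 3,744 | 3.8% | 4% | 7.31 | 7.17 |
| 0.35 | 60 | 819 | 4,419 | 18.5% | 23% | 7.95 | 7.17 |
| 0.50 | 90 | 2,025 | 5,625 | 36.0% | 56% | 8.96 | 7.17 |

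The share of variance and the gain in patients are different quantities. In the middle case they are 18.5% and 23%.

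**In terms of power.** Let D be the difference between approaches in within-approach SDs. The unadjusted SE is larger by the factor √(1 + p(1−p)D²). Take an effect for which the adjusted analysis has 80.0% power at 140 per arm:

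| p | D | SE inflation | Power, unadjusted |
|---|---|---|---|
| 0.1 | 0.25 | 0.3% | 79.8% |
| 0.3 | 0.5 | 2.6% | 78.0% |
| 0.3 | 1.0 | 10.0% | 72.1% |
| 0.5 | 1.0 | 11.8% | 70.7% |

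Over p 0.1 to 0.5, the loss is under 3 points when D is 0.5 or less, and about 3.5 to 9 points at D = 1.

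**Validity.** In 10,000 simulated trials (p = 0.3, D = 1, 140 per arm) the type I error was 5.2% unadjusted and 4.7% adjusted. Power was 71.9% and 79.7%.

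**Chance imbalance.** In the middle case, under simple randomization, the SD of the between-arm difference in approach share is √(2·0.35·0.65/140) = 0.057. Multiplied by 60 min this is 3.42 min. The gap between the two SEs is √(63.13 − 51.43) = √11.70 = 3.42 min. The two agree: the unadjusted SE already contains the variation due to chance imbalance, which is not a further error.

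**The case against.** The strongest case against is that nothing here is wrong. The named tests are valid, covariates for secondary endpoints commonly belong in an analysis plan, and such a plan may exist although it is not shown. The article's sentence does not exclude an adjusted analysis. All this stands, and the point is therefore one of efficiency. It remains usable because the article does name a test, and a better one is available at little cost.

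Three further objections carry weight.
- **The size rests on outside assumptions.** The upper end needs a 90-min difference against a 60-min SD, which is 1.5 SD, with an even mix. For blood loss and length of stay there is no calculation in the outcome's own units.
- **Centre stratification may partly balance approach**, if approach follows local expertise. This limits chance imbalance. It does not restore precision under the stated tests, because they ignore centre too and leave the balanced variation in the error term.
- **Approach is not a clean category.** The laparoscopic section allows a Pfannenstiel incision for clamping before randomization, and for transection in either arm afterwards. A model needs a rule for such cases.

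A reader might infer that the unadjusted comparison is biased, or that an imbalance in approach would go unaccounted for. The documents do not support this. Randomization protects the type I error, and the standard error allows for chance imbalance.

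**Conclusion.** The point holds as a minor gain in efficiency on three secondary endpoints. The primary endpoint, its chi-squared test and the sample size are unaffected.

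A reader might also infer that precision is certainly lost. The documents support only a conditional statement, because they give neither the mix of approaches nor their effect on any outcome. Under the operating-time assumptions above, the 95% half-width in the middle case falls from 1.96 × 7.95 = 15.6 min to 1.96 × 7.17 = 14.1 min. At the low end of the ranges the benefit is too small to matter. The calculation credits approach alone and counts no gain or cost from adding centre to the model.

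**What to change.** In the statistics section, for operating time, blood loss and length of stay, replace the unadjusted test as the main analysis with a linear model, on the log scale where the outcome is skewed. The model contains:
- arm;
- centre, as the stratification factor;
- surgical approach at the moment of randomization, with a prespecified category for hybrid or Pfannenstiel cases.

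Conversions after randomization do not change a patient's category, so that nothing allocation may have caused is adjusted away. Keep the t-test or Mann-Whitney U as a supporting analysis. Fix the scale and the categories before the data are analysed. On the log scale the result is a ratio, and should be reported as such.

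**Cost.** The change is a sentence or two of analysis wording, with no extra patients or visits, and the model runs in the stated software. There are two small burdens. First, it must be confirmed that approach at randomization is captured by the type-of-surgery item or the registry's operative record; if not, one field is added to the form. Second, with 18 hospitals and 340 patients the average is about 19 per hospital (340/18), so small centres may need pooling under a rule set in advance.
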